### Sample size and power

The pre-post design, with at least 366 eligible and enrolled participants [28] and 5% loss to follow-up (LTF) after 12 months, will have over 90% of power to detect the primary effectiveness endpoint of this trial, of 31.5% or greater, compared to the 21% change in the control group seem previously in a South Asian population [29]. For the analysis of two randomized groups (CO and CB arms), with 320 participants, we will be able to detect a relative risk of 1.5 given 0.315 risk probability in the control group, 5% LTF rate with 80% power and 5% level of significance [30].

In the secondary analysis, where we will compare the within-participant changes in HbA1c, systolic and diastolic blood pressure, and lipids observed in the cafeteria intervention to those observed in the behavioral intervention. Given the sample sizes of 366 and 320 respectively, 5% LTF rate with 80% power and 5% level of significance, we will be able to detect the minimum differences as presented in Table 3. For the before-after design, we considered three possible values of the correlation (*ρ* = 0.5, 0.6, 0.7) between repeated measurements during the control period and during the intervention period.

**Table 3 Tab3:** Minimum absolute detectable differences for the change in glycosylated hemoglobin, systolic and diastolic blood pressure, and triglyceride for sample sizes of 366 and 320 correspondingly, 5% loss-to-follow-up rate with 80% power and 5% level of significance, for the Nepal Pioneer Worksite Intervention Trial

		Minimum absolute detectable difference			
		*N* = 366			*N* = 320
Parameter	Std. Dev.	*ρ*^∗^=0.5	*ρ*^∗^=0.6	*ρ*^∗^=0.7	Independent samples
Glycated hemoglobin, %	0.38	0.06	0.05	0.045	0.12
Diastolic blood pressure, mmHg	9.43	1.4	1.3	1.1	3
Systolic blood pressure, mmHg	13.32	2	1.8	1.6	4.3
Triglycerides, mg/dL	82.47	12.5	11.2	9.7	26.6

*Correlation between the changes of the same individual observed during control and treatment periods of time

Standard deviations are calculated from the baseline data of the study participants

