### Follow up

We will assess outcomes at 6 months (at the end of the control period), 12 months (at the end of the cafeteria intervention), and 18 months (at the end of the behavioral intervention). During each follow up, fasting blood samples will be collected and analyzed for HbA1c, fasting glucose, and lipid profile (HDL, LDL, total cholesterol, triglycerides). We will re-administer the global physical activity questionnaire, and the two 24-h diet recalls. We will re-measure height, weight, waist circumference, and blood pressure at each of these time points as well.

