#### Effectiveness of the behavioral intervention

At the 18-month follow-up, we will compare the proportion of participants who have achieved two or more of their cardio-metabolic risk factor reduction goals in CO arm to the proportion of participants in the CB arm using a *χ*^2^ test. In the event that randomization does not appear to have controlled for differences between the treatment and control groups on baseline characteristics, in secondary analysis, we will statistically control for those differences using the GEE approach with the binary distribution, logit link function and an exchangeable working correlation structure [27].

Our secondary analysis will compare the change in HbA1c, systolic blood pressure, and lipids during the cafeteria-only intervention to the change during the control period using a paired t-test. Similarly, we will compare the change in HbA1c, systolic blood pressure, and lipids between CO group and CB group using a paired t-test. Assumptions of the statistical tests will be examined and if violated non-parametric testing will be explored. In the event that randomization does not appear to have controlled for differences between the treatment and control groups in baseline characteristics, we will conduct the GEE approach with the Gaussian distribution, identity link function and an exchangeable working correlation matrix [27] to adjust for potential confounding factors. The data will be analyzed using STATA-15.

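### Table 3 gives ρ two incompatible meanings, and its N = 366 columns use a variance that fits a single two-visit change, not the planned comparison of two adjacent changes sharing month 6

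*Protocol article*

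**What the plan says.** The data analysis plan (Protocol article, Effectiveness of the behavioral intervention) has a secondary analysis for the pre-post stage. It compares the change in HbA1c, systolic blood pressure and lipids during the cafeteria-only period "to the change during the control period using a paired t-test". The Follow up section fixes the visits: "We will assess outcomes at 6 months (at the end of the control period), 12 months (at the end of the cafeteria intervention". Month 6 therefore closes the control change and opens the cafeteria change.

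Sample size and power states that with 366 and 320 participants, "5% LTF rate with 80% power and 5% level of significance, we will be able to detect the minimum differences as presented in Table 3". The pre-post columns take ρ as 0.5, 0.6 and 0.7, and the section gives ρ two meanings:

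- in the text, a correlation "between repeated measurements during the control period and during the intervention period";
- in the Table 3 footnote, "Correlation between the changes of the same individual observed during control and treatment periods of time".

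The second footnote adds: "Standard deviations are calculated from the baseline data of the study participants". No SD of change and no observed correlation between visits is given.

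**The concern.** Under the footnote, ρ is a clearly positive correlation between two changes that share the month-6 value, which enters one with a plus sign and the other with a minus sign. Under the usual correlation structures two such changes are negatively correlated. Under the text, ρ relates measurements, but the formula behind the table then leaves out part of the variance of a difference between two changes. Either way the printed differences would be too small for the stated test at the stated ρ. A reader would credit the pre-post stage with 80% power for about 2 mmHg systolic or 12.5 mg/dL triglycerides, and could take a null secondary result as stronger evidence than it is.

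**Working it through.** **Inputs** (all from Sample size and power): N = 366; 5% loss, so n = 366 × 0.95 = 347.7; 80% power; 5% significance level. Sidedness is not stated; two-sided is assumed because it reproduces the table, giving z = 1.96 + 0.84 = 2.80. Baseline SDs: HbA1c 0.38, DBP 9.43, SBP 13.32, triglycerides 82.47.

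**1. Reproducing the table.** Detectable difference = 2.80 × SD × √(2(1−ρ)) / √347.7. For SBP at ρ = 0.5: 2.80 × 13.32 × 1 / 18.65 = 2.00.

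| | Printed (ρ 0.5/0.6/0.7) | Formula |
|---|---|---|
| HbA1c, % | 0.06/0.05/0.045 | 0.057/0.051/0.044 |
| DBP, mmHg | 1.4/1.3/1.1 | 1.42/1.27/1.10 |
| SBP, mmHg | 2/1.8/1.6 | 2.00/1.79/1.55 |
| Triglycerides, mg/dL | 12.5/11.2/9.7 | 12.4/11.1/9.6 |

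Triglycerides differ by about 1%; the rest agree to rounding.

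**2. Variance of the planned contrast.** (Y12 − Y6) − (Y6 − Y0) = Y12 − 2·Y6 + Y0. With equal variances, its variance is SD² × [6 − 4r(0,6) − 4r(6,12) + 2r(0,12)].

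- Equal correlation r: 6(1−r)·SD².
- AR(1), with r(0,12) = r²: 2(1−r)(3−r)·SD².

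The table uses 2(1−ρ)·SD². If ρ relates measurements, that is the variance of one two-visit change.

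**3. The text's reading, r = 0.5/0.6/0.7.** The factor over the table formula is √3 = 1.73 (equal correlation) or √(3−r) = 1.58/1.55/1.52 (AR(1)).

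| | Equal correlation | AR(1) |
|---|---|---|
| HbA1c | 0.099/0.088/0.077 | 0.090/0.079/0.067 |
| DBP | 2.45/2.20/1.90 | 2.24/1.96/1.66 |
| SBP | 3.47/3.10/2.69 | 3.16/2.77/2.35 |
| Triglycerides | 21.5/19.2/16.6 | 19.6/17.2/14.6 |

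Power at the printed SBP differences is Φ(difference × √347.7 / SD of contrast − 1.96). At r = 0.5 with equal correlation: 2 × 18.65 / (13.32 × √3) − 1.96 = −0.34, so 37%. Across the three columns power is 37 to 39% (equal correlation) and about 43 to 48% (AR(1)).

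**4. The footnote's reading.** Here the table SD stands for the SD of a change and ρ for the correlation between the two changes. With equal variances, SD of change = √(2(1−r))·SD, so equating it to the baseline SD forces adjacent visits to correlate at 0.5. The correlation between the changes is then 0.5 + 0.5 − 1 − r(0,12) = −r(0,12). A value of +0.5 requires r(0,12) = −0.5, the lowest value the correlation matrix allows (2 × 0.5² − 1 = −0.5). Values of +0.6 and +0.7 are impossible.

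If the true correlation between changes is c, the factor is √((1−c)/(1−ρ)). For c from −0.15 to −0.5 this is 1.52–1.73, 1.70–1.94 and 1.96–2.24 in the three columns.

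**5. When the printed values would be reached.**

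- Equal correlation: 6(1−r) = 2(1−ρ), so r = 1 − (1−ρ)/3 = 0.83/0.87/0.90.
- AR(1): (1−r)(3−r) = 1−ρ, so r = 2 − √(2−ρ) = 0.78/0.82/0.86.

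For SBP, r = 0.8 gives 2.19 (equal correlation) or 1.88 (AR(1)); r = 0.9 gives 1.55 or 1.30.

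**The case against.** Four points can fairly be made for the plan.

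- **The true correlation is unknown.** The protocol offers 0.5 to 0.7 only as possible values. If visits correlate above about 0.8 to 0.9, the shortfall disappears. This stands, so a reader who infers that the trial cannot detect 2 mmHg goes too far. The conclusion is conditional on the protocol's own range.
- **A negative correlation between the changes is not a mathematical necessity.** It is −0.5 under equal correlation and −0.25 to −0.15 under AR(1) with r = 0.5 to 0.7, but it turns positive if r(0,12) < r(0,6) + r(6,12) − 1. This stands, but it does not rescue the table: with adjacent visits correlating at 0.7, +0.5 would need a baseline to month-12 correlation of only 3 × 0.7 − 2 = 0.1.
- **The baseline SD can be a cautious stand-in for the SD of a change.** When r exceeds 0.5, the SD of a change is smaller. At r = 0.7 it is √0.6 = 0.77 of the baseline SD, which brings the factor of 2.24 down to 1.73. The upper end of the footnote range therefore depends on keeping the table's SD.
- **Nothing in the conduct or inference depends on Table 3.** A paired t-test uses the observed variance of the differences, so its p-value and confidence interval stay valid. Nor does the document say that null secondary results will be judged against the table.

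A reader might also infer that the main sample size is undermined. The documents do not support that: the primary power statement is for a binary endpoint and separate, and this point does not touch the N = 320 column.

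**Conclusion.** The N = 366 columns of Table 3 do not match the test the protocol plans under either of its definitions of ρ. The arithmetic reproduces; the fault is the variance behind it.

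On the text's reading, with r = 0.5 to 0.7, equal variances over time and a two-sided test, the printed differences are too small by a factor of 1.73 (equal correlation) or 1.52 to 1.58 (AR(1)). On the footnote's reading, the assumed correlations are implausible or impossible, and the factor is about 1.5 to 2.2. The two ranges rest on different premises and should not be merged: the figure of 1.5 to 1.7 belongs to the text's definition, not the footnote's.

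This should be corrected, but its weight is moderate: it concerns planning figures for secondary continuous outcomes only.

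**What to change.** 1. Define ρ once, identically in the text and the footnote, as the correlation between measurements on the same person.
2. State the assumed correlation structure, or give the SD of the difference of changes directly. The documents do not settle which structure applies, so no single formula should be imposed without saying so.
3. Recompute the 12 cells of the N = 366 columns from Var(Y12 − 2·Y6 + Y0): 6(1−r)·SD² under equal correlation or 2(1−r)(3−r)·SD² under AR(1).
4. Show the results over a range of r that extends beyond 0.7, so that the reader sees where the present values would be reached, and restate the detectable differences in the text.

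The cost is 12 table cells, one footnote and one sentence of text. At r = 0.5 to 0.7 the stated differences become less favourable. Sample size, visits, endpoints and the planned test do not change.

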### Minimization of contamination

The risk and level of contamination during the randomized study phase for the behavioral intervention will be monitored at the participant level. The participants will be instructed not to share information about the study and not to provide any support to people in their worksite, other than their classmates. The behavioral classes will be conducted in a separate building outside of their workspace to ensure privacy. Further, we will measure possible contamination by asking if the participants have received any information / advice regarding diet and lifestyle changes from any of their peers and if they did, collect the name and contact information of the peer. If the contamination is found to be significant, we will make adjustments by adding the contamination as a variable in the final model while estimating the effect in secondary analysis.

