#### Step 2: The behavioral intervention

After 6 months of the cafeteria intervention, half of the participants will be randomized using computer generated random numbers to receive a cafeteria and behavioral intervention (CB), the other half of the participants will continue to receive the cafeteria only (CO) intervention. The behavioral intervention will be comprised of intensive education sessions, group counseling, and goal setting and monitoring exercises based on the Diabetes Prevention Program (DPP) [24] tailored to local needs. The curriculum includes 24 sessions of 16 core weekly sessions during the first 4 months of this phase of the intervention followed by 8 weekly maintenance sessions. Each session will be 1 h long, and will be facilitated by a dietitian. Broadly, the curriculum covers subject matters of importance for achieving and maintaining healthy weight, eating a healthy diet, increasing physical activity, stress management, and overcoming common challenges encountered when making lifestyle changes. Similar to the cafeteria intervention, healthy eating messages include increasing fresh fruits and vegetable intake, avoiding added sugar, choosing whole grains, choosing healthier sources of protein, reducing sodium, and monitoring portion sizes. Participants will be encouraged to keep food and activity diaries throughout the course of the study. The maintenance period’s focus will be on overcoming declines in motivation and maintaining long-term healthy behaviors. All of the sessions will be conducted at the worksite during the workday. There will be about 20 participants in each education class. Participants will set a minimum of two lifestyle-change goals (e.g. Half of their total grain intake will be whole grains, walking 30 min a day, or reducing 7% of their body weight).

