#### Data analysis plan

The primary analysis will be intention to treat. The quantitative data analysis will follow the Consolidated Standards of Reporting Trials (CONSORT) guidelines [26]. The flowchart will include the number of participants seen at each stage, including the number screened, eligible, randomized, and analyzed for the primary outcomes.

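### Secondary analysis only: adjusting for self-reported peer advice, a variable measured after randomisation and dependent on arm, can bias the CO versus CB estimate, and the trigger for doing so is undefined

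*Protocol article*

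**What the plan says.** All references are to the protocol article.

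- **Timing and level** (Minimization of contamination): "The risk and level of contamination during the randomized study phase for the behavioral intervention will be monitored at the participant level". Contamination is therefore a post-randomisation measurement.
- **Measure** (same section): it is obtained by "asking if the participants have received any information / advice regarding diet and lifestyle changes from any of their peers". If the answer is yes, the peer's identity is also collected. Participants are told to support nobody at the worksite except their classmates.
- **Rule** (same section): "If the contamination is found to be significant, we will make adjustments by adding the contamination as a variable in the final model". Read to its end, the clause is "adding the contamination as a variable in the final model while estimating the effect in secondary analysis". The closing words confine the rule to secondary analysis. Neither the meaning of significant nor the coding of the variable is given.
- **Randomisation and format** (Step 2: The behavioral intervention): "half of the participants will be randomized using computer generated random numbers"; the CB arm then has weekly group sessions, and "There will be about 20 participants in each education class".
- **Primary analysis**: "The primary analysis will be intention to treat" (Data analysis plan). The test compares the proportion "in CO arm to the proportion of participants in the CB arm using a" chi-square test (Effectiveness of the behavioral intervention), with no contamination term.

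**The concern.** A covariate measured before randomisation can be adjusted for safely. One measured afterwards, and changed by the allocation, cannot in general. Three features of this variable matter.

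1. **It depends on arm.** The question covers advice from any peer and is put to participants without regard to arm. A CB participant who talks with classmates, which the plan allows, can truthfully answer yes.
2. **In CB it partly measures the intervention.** That yes reflects delivery as designed, not leakage between arms.
3. **It may share causes with the outcome.** Motivated people may both seek advice and improve more. Comparing arms within levels of the answer then compares people who differ in motivation.

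The estimate at stake is the secondary CO versus CB effect, which a reader would take as corrected for contamination. The trigger adds a second problem: whether the adjusted figure appears depends on an unspecified test or judgement made on the trial's own data.

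**Working it through.** **Figures that do not change.** The stated power for CO versus CB is 80% with 320 randomised, control risk 0.315, relative risk 1.5 and 5% loss. With 160 × 0.95 = 152 per arm and risks 0.315 and 0.315 × 1.5 = 0.4725, a two-sided 5% test has 80.6% power. The stated figure reproduces, and nothing below alters it.

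**Inputs for the illustrations.** From Table 3: systolic SD 13.32 mmHg, and 4.3 mmHg as the minimum detectable CO versus CB difference. Assumed, because the article gives no values: the proportions answering yes (p0 in CO, p1 in CB), the effect of contamination, and the strength of any shared cause.

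**Formula.** In a linear model with arm and the contamination indicator C:

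adjusted difference = unadjusted difference − s × (p1 − p0),

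where s is the pooled within-arm slope of outcome on C, weighting each arm by p(1 − p).

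**Case 1: a real effect, no shared cause.** True effect −4.3; p0 = 0.30; contaminated CO participants get half the effect (−2.15); C has no effect in CB.

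- Unadjusted: −4.3 + 0.30 × 2.15 = −3.655.
- p1 = 0.95: weights 0.30 × 0.70 = 0.21 and 0.95 × 0.05 = 0.0475; s = −2.15 × 0.21/0.2575 = −1.753; adjusted = −3.655 + 1.753 × 0.65 = **−2.52**.
- p1 = 0.70: weights 0.21 and 0.21; s = −1.075; adjusted = −3.655 + 1.075 × 0.40 = **−3.225**.
- C coded in CO only (p1 = 0): s = −2.15; adjusted = −3.655 − 2.15 × 0.30 = **−4.30**.

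In the first two settings the adjusted value lies further from −4.3 than the unadjusted one. In the third, adjustment recovers the effect without contamination.

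**Case 2: no true effect, shared cause.** C arises from a latent normal variable correlated 0.5 with a trait that lowers systolic pressure by 0.3 SD per SD. The within-arm covariance of outcome and C is −0.3 × 13.32 × 0.5 × φ = −1.998 × φ, where φ is the normal density at the cut-point: 0.3477 for 30% or 70%, 0.1031 for 95%, 0.1755 for 10%. With p0 = 0.30:

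| p1 | pooled slope s | adjusted difference, mmHg (truth 0) |
|---|---|---|
| 0.70 | −1.998 × 0.6954/0.42 = −3.31 | **+1.32** |
| 0.95 | −1.998 × 0.4508/0.2575 = −3.50 | **+2.27** |
| 0.10 | −1.998 × 0.5232/0.30 = −3.48 | **−0.70** |

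The sign depends on which arm answers yes more often.

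**The binary primary endpoint, analysed with this adjustment.** Large simulations (1,000,000 participants, assumed rates) show the same pattern in the risk difference:

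| Setting | Unadjusted | Adjusted |
|---|---|---|
| No effect; yes in 24% CO, 58% CB; strong shared cause (log-odds 1.0 per SD) | 0.00 | −0.055 |
| No effect; yes in 21% CO, 59% CB; weaker shared cause (0.5 per SD) | 0.00 | −0.02 |
| Real effect; strong shared cause | 0.133 | 0.075 |
| Peer support carries part of the effect; 20% CO, 60% CB | 0.157 | 0.116 |
| CO-only contamination (20%), no shared cause | 0.141 | 0.157 |
| No effect; C independent of arm | 0.00 | 0.00 |

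The bias therefore needs C to depend on arm and also either to share causes with the outcome, to carry part of the effect, or to be coded in CB where it is not leakage.

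**The case against.** The strongest reply has four parts.

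- **It is only secondary.** This stands. A reader who stops before the end of the sentence might infer that the main randomised comparison is conditioned on contamination. The documents do not support that: the primary test is intention to treat and has no contamination term.
- **Bias is not certain.** This also stands. With CO-only coding and no shared cause, adjustment gives −4.30 exactly; with C independent of arm and no true effect, it does no harm. To say that the adjustment necessarily biases the estimate, or can never recover the uncontaminated effect, would go too far.
- **The coding is left open.** Because the advising peer's identity is collected, advice passing from CB to CO could be separated out, and a fuller document might do so. This is a fair mitigation. But the only measure the article states is advice from any peer, in either arm, and even CO-only coding leaves the shared-cause problem.
- **The usual replacement has its own flaw.** In Case 1, an instrumental-variable estimate with binary receipt (100% of CB assumed, 30% of CO) is −3.655/0.70 = −5.22. Its error of 0.92 exceeds the unadjusted contrast's 0.645. Half-dose coding gives −3.655/(1 − 0.15) = −4.30, but requires the dose to be known. This stands, so such an analysis can only be an optional sensitivity analysis.

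**Conclusion.** Wrong as written, low severity. The rule adjusts a randomised contrast for a post-randomisation variable that, as worded, depends on arm and partly records the intervention. It can bias the secondary CO versus CB estimate in either direction, and it does not in general give the effect without contamination. The trigger is undefined and data-driven.

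The size is unknown. The illustrations run from an apparent difference of −0.70 to +2.27 mmHg where none exists, and to −2.52 in place of −4.3. They rest on assumed reporting rates, dose and shared-cause strength; a different choice gives a different size or no bias. The primary test, sample size, power and significance level are unaffected. Nor does the article say that the adjusted figure would replace the intention-to-treat result, so that should not be inferred.

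**What to change.** 1. Delete the sentence that adds contamination to the model, together with its significance trigger.
2. Keep the randomised contrast, not adjusted for contamination, as the reported effect in secondary as well as primary analyses. For the primary analysis this is already the plan. Adjustment for baseline characteristics is a separate matter and is not touched.
3. Report contamination descriptively by arm, counting as contamination only advice that CO participants received from CB participants. Matching the named peer to the allocation list is enough; advice between CB classmates can be shown separately as part of delivery.
4. Only if a contamination-corrected effect is wanted, prespecify an instrumental-variable sensitivity analysis with randomised arm as the instrument, run whatever any test shows. State its assumptions, including that binary receipt overstates the effect when contamination is only a partial dose.

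Items 1 to 3 cost a short rewording and one table, using data already planned for collection. Item 4 costs one further analysis with a wider interval than the intention-to-treat estimate.
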